#### Usual care (control group)

Patients in the control group will have usual scheduled outpatient follow-up visits at the hospital initiated by the physician every 3 months. Scheduled appointments will be pre-booked in the patients’ hospital charts at the initiation of study to ensure the pre-specified intervals. These patients do not use the clinical PRO questionnaire, but complete the research questionnaires. They have blood tests, blood pressure and weight measured in the outpatient clinic as usual practice.

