**Fig. 2 Fig2:**
[figure not shown]
Flowchart following patients from introduction through inclusion and to final data collection

**Table 1 Tab1:** Complete overview of the questionnaires used in the PROKID project

Name	Introduction	Baseline	Clinical questionnaire	Research questionnaire
Purpose	Identify determinants for patients choosing PRO-based follow-up	Baseline characteristics	Using questionnaire as screenings tool and dialogue support	Repeated measures of characteristics
Respondents	ALL newly referred patients in renal outpatient clinic	ALL enrolled patients in PROKID study	Participants in PRO-based follow-up and in PRO-based telephone consultation arm	ALL patients in the three randomisation groups
Content	• Renal-specific items • SF-GH1 • HLQ^a^ (subscale 4,6,9) • Self-efficacy^b^ • PAM^c^(2 + 12) • Demographic • Consent (Yes/no)^h^	• Renal-specific domains • SF-GH1^d^ • EQ-5D^e^ • BIPQ^f^	Renal-specific domains • KDQOL-SF^g^ • EORTC • SF-GH1 • Need/wish for consultation • Free textbox	• Self-efficacy • EQ-5D • BIPQ • Patient involvement • Confidence • Satisfaction
No items	36	37	29	27

^a^ Health Literacy Questionnaire, ^b^ General Self-efficacy Scale (GSE), ^c^ Patient Activation Measure, ^d^ Short Form 36_GH1, ^e^ Euroqol Quality of Life, ^f^ Brief Illness Perception Questionnaire, ^g^ Kidney Disease Quality of Life Short Form,^h^ Consent to allow the researchers to obtain data on blood samples from the medical record

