### PRO research questionnaire

The PRO research questionnaire covers a range of scales and items, which is shown in Table 1. Patients will answer this questionnaire at 0-, 6-, 12- and 18-month follow-up. Modes of administration will be electronic and paper version questionnaires collected in the patients’ own homes. The questionnaire will be obtainable in a Danish version and should always be completed by the patient, with possible assistance from a family member or friend. At baseline, the patient will answer the questionnaire on an iPad or on a paper version in the outpatient clinic. At the end of study or if a patient exits the study, he or she will be contacted and asked to answer the questionnaire. To minimise missing data, non-responders get two reminders after 4 and 7 days. The acceptable PRO assessment time window is 1 month. Patients’ responses to this questionnaire will not be available to the clinicians.

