### Outcomes

The effects of using PRO as the basis for follow-up will be evaluated with regard to three different aspects: clinical outcomes, health resource utilisation and patient-reported outcomes. Clinical outcomes include pivotal clinical quality measures (mortality, renal function, initiation of dialysis, hospitalisation). Health resource utilisation will be measured by number of contacts to the nephrology outpatient clinic (Table 2) and the patient-reported outcomes will be measured with regard to: quality of life, illness perception, patient activation, satisfaction and confidence towards the outpatient follow-up. An overview of primary and secondary outcomes and data sources is shown in Table 2.

**Table 2 Tab2:** Primary and secondary outcomes, data sources and timeline for measurements

**Outcomes**	**Data source**	**Measurement/month**

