**Patient-reported outcomes**		
Quality of life	Euroqol (EQ-5D 5 L)	0,6,12,18
General health	Short Form-36 (SF-36)	0,6,12,18
Illness perception	Brief Illness Perception (IPQ-B)	0,6,12,18
Self-efficacy	General Self-efficacy (GSE)	0,12,18
Patient involvement	AmbuFlex PRO questionnaire	6,12,18
Confidence, satisfaction	AmbuFlex PRO questionnaire	6,12,18

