#### Patient-reported outcomes

Quality of life (QOL) will be measured by EuroQol EQ-5D-5 L [36]. The EQ-5D-5 L questionnaire measures individual generic health status using five dimensions: mobility, self-care, usual activities, pain/discomfort, and anxiety/depression, and each dimension has five levels depending on severity of symptoms (1 no problems, 5 extreme problems) and a visual analogue scale. The scores can then be converted into a single index number. The index value will be used for calculation of quality-adjusted life years for a health economic analysis of the intervention, which will be conducted after completion of this study. The EQ-5D scale is favoured for use in patients with chronic kidney disease due to ease of use for patients [37]. Illness perception will be measured by the IPQ-B (Brief Illness Perception Questionnaire), which comprises five components. Each of these components holds a perception about one aspect of the illness, and together they provide an individual’s coherent view of an illness [38]. The IPQ-B is widely used and has sound psychometric properties [39].Self-efficacy will be measured by using the Danish version of General Self-Efficacy Scale (GSE) [40, 41]. GSE was designed to assess optimistic self-belief to cope with difficult demands in life [40, 41]. GSE includes 10 items with a response range from 1 “not at all true” to 4 “exactly true”. The GSE scale has been used in a range of research projects in different countries and populations, where it typically yielded sufficient psychometric properties [42]. Confidence, safety and satisfaction will be measured by using ad hoc items developed from the Danish PREM (Patient-Reported Experience Measure) questionnaire from the Danish Cancer Society.

All outcomes will be compared in the three groups and measured at baseline and after 6, 12 and 18 months of follow-up or at the time a patient leaves the study due to patient wish, death, transplantation or initiation of dialyses.

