### Statistical methods

The three randomisation groups will be compared in intention-to-treat analysis and per protocol as recommended in non-inferiority trials [48]. The primary comparison groups will be composed of those receiving usual care, versus each of the intervention groups separately. Analysis methods will be chosen according to the data type of the outcome under investigation.
*Continuous endpoints (*e.g. *quality of life, estimated Glomerular Filtration Rate)*: These data will be summarised using means and standard deviations, with differences in means and 95% confidence intervals reported. Longitudinal plots of the data over time will also be constructed for visual presentation of the data. The primary analysis will be adjusted for covariates identified as potentially prognostic variables (e.g. sex and age) in a multiple linear regression model. A secondary unadjusted analysis will also be performed if covariate adjustment is not practical (e.g. due to low event rates).*Categorical (dichotomous) endpoints (*e.g. *PRO data, hospitalisation rates)*: For dichotomous secondary endpoints, the proportion of participants and percentages will be summarised between arms. Logistic regression will be used to produce estimates of relative risks and 95% confidence intervals.*Time-to-event endpoints (*e.g. *time to initiation of dialysis, mortality):* These endpoints will be modelled for each randomisation arm using survival analysis methods. Kaplan–Meier survival curves will be constructed for visual presentation of time-to-event comparisons. The primary analysis will be carried out using a Cox proportional hazards or an extended Cox model to include prognostic covariates. Hazard ratios will be produced with 95% confidence intervals.

Sensitivity analyses will be performed to test the robustness of the results in the presence of differences in the groups.

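### General health is listed as a three-arm follow-up outcome, but by Table 1 usual care has no form that measures it after baseline; patient activation is named as an outcome but measured only before enrolment

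*Protocol article*

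**What the plan says.** **What is promised.** In the protocol article, Table 2 (Outcomes) gives general health a row with the SF-36 as data source and measurement at months 0, 6, 12 and 18. The Patient-reported outcomes subsection adds: "All outcomes will be compared in the three groups and measured at baseline and after 6, 12 and 18 months of follow-up". Under Statistical methods, "The primary comparison groups will be composed of those receiving usual care, versus each of the intervention groups separately".

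**What is collected.** Table 1 (Study timeline) sets out four forms. SF-GH1, which its footnote identifies as the first general-health item of the SF-36, is in the introduction, baseline and clinical questionnaires. The respondents of the clinical questionnaire are "Participants in PRO-based follow-up and in PRO-based telephone consultation arm". The content of the research questionnaire, which goes to all three arms, is "Self-efficacy • EQ-5D • BIPQ • Patient involvement • Confidence • Satisfaction". Its timing is given under PRO research questionnaire: "Patients will answer this questionnaire at 0-, 6-, 12- and 18-month follow-up". For usual care the protocol states: "These patients do not use the clinical PRO questionnaire, but complete the research questionnaires".

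**Patient activation.** The Outcomes section says that patient-reported outcomes cover "quality of life, illness perception, patient activation, satisfaction and confidence towards the outpatient follow-up". Table 2 has no activation row. Table 1 shows the activation items (PAM) in the introduction questionnaire only. Other measurements describes that form as given before study entry and uses its data to compare participants with those who decline or drop out.

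**The concern.** An outcome that is to be compared with usual care has to be measured in usual care. If controls never receive the general-health item after baseline, the two contrasts that the plan calls primary (each PRO arm against usual care) cannot be estimated for this outcome, and no later choice of analysis can recover answers that were never collected.

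The data that would exist in the PRO arms also differ in kind. The clinical questionnaire is read by the treating physicians and, in the remote arm, helps decide whether the patient is contacted. The research questionnaire is withheld from them. A patient may answer a general-health item differently when the answer can trigger a call or a visit.

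Activation raises a smaller question of the same type: it is named among the outcomes used to judge the effect of PRO-based follow-up, but it has no measurement on which an effect could show.

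**Working it through.** There is no figure to reproduce; the check sets the two tables side by side.

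**Step 1. Content of each form, from Table 1, with timing from the text.**

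| Form | Respondents | Timing | SF-GH1 | Activation items |
|---|---|---|---|---|
| Introduction | all newly referred patients | before entry | yes | yes |
| Baseline | all enrolled patients | month 0 | yes | no |
| Clinical | the two PRO arms | every 3 months | yes | no |
| Research | all three arms | months 0, 6, 12, 18 | no | no |

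**Step 2. General health by arm.**

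| Arm | Month 0 | Months 6, 12, 18 |
|---|---|---|
| PRO-based remote follow-up | yes | yes, clinical form |
| PRO-based telephone consultations | yes | yes, clinical form |
| Usual care | yes | no listed source |

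**Step 3. Contrasts after baseline.** Remote against usual care: not estimable. Telephone against usual care: not estimable. Remote against telephone: possible, on the clinical form.

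**Step 4. Size.** The sample-size paragraph plans 50 patients per group. Table 2 has three follow-up times for general health, so 50 × 3 = 150 control values are planned before attrition. If Table 1 is right, 0 of the 150 are collected. If Table 2 is right and Table 1 has merely dropped an item from the research column, the plan loses none. The documents do not settle which table is correct.

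**Step 5. Activation.** The items are available before randomisation for all newly referred patients. After randomisation they are on no form in any arm.

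**Step 6. Instrument name.** Table 2 names the SF-36. The only SF-36 general-health item shown in Table 1 is SF-GH1, so the two tables do not describe the outcome in the same way.

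**The case against.** The best defence is that this is a slip in a table rather than a gap in collection. Table 2's times for general health match the research questionnaire exactly, whereas the clinical form is 3-monthly. The text says that every outcome is compared in three groups. The tables are loose elsewhere: hospitalisation is scheduled at months 16, 12 and 18, and self-efficacy at 0, 12 and 18 although its form also goes out at month 6. The questionnaires themselves are not shown. So a reader might infer that all control values are certain to be missing, or that the sponsor chose to leave the item out for controls; the documents establish neither. What stands against the defence is that Table 1 is titled a complete overview and lists content form by form, so someone building the forms from it would omit the item for controls.

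The 27-item count does not decide the matter. Self-efficacy takes 10 items and EQ-5D takes 5 + 1 = 6, leaving 27 − 16 = 11 for illness perception, involvement, confidence and satisfaction. The article gives no item counts for those four, so the total neither excludes nor confirms SF-GH1.

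Two wider readings also fail. One is that general health cannot be compared between any arms: both PRO arms answer SF-GH1 and could be compared with each other. The other is that nobody receives the activation items: all newly referred patients do, before enrolment.

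On activation, the defence is largely right. Table 2 is presented as the overview of outcomes and omits it, and the stated use of the items is properly served by collecting them before enrolment.

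The stakes are also limited. Neither outcome is in the three hypotheses, the Abstract names EQ-5D and BIPQ as the main PRO measures, and the EQ-5D visual analogue scale gives a related self-rating in all arms. That lowers the importance but does not supply the outcome that Table 2 lists.

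**Conclusion.** The point holds as an internal contradiction with a practical consequence. Followed as written, the plan gives no general-health value for usual care after baseline, so this outcome cannot be compared with usual care at 6, 12 or 18 months. The comparison that remains, remote against telephone, is not the one the plan calls primary and would rest on a form that clinicians act on. This conclusion assumes that Table 1 reports the content of the research questionnaire correctly; if it does not, the error is in Table 1 and only the text needs correcting.

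Activation is a separate and smaller inconsistency: one mention in the Outcomes section, no row in Table 2, and no value in any arm after randomisation. It does not follow that activation should be added at follow-up.

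Both are secondary outcomes. The primary eGFR analysis is unaffected, and EQ-5D and BIPQ are collected in all three arms on the research form.

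**What to change.** First check the research questionnaire in use. If SF-GH1 is already on it, correct Table 1. If it is not, choose one of two courses.

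1. Add SF-GH1 to the research questionnaire at 6, 12 and 18 months for all three arms, and state that the between-arm analysis uses only that form. The cost is one more item on a 27-item form, or three more answers per patient over the study. PRO-arm patients would answer it on both forms around those months. Inclusion began in January 2019, so the first 6-month assessments fell due in July 2019; any that passed without the item are lost.
2. Delete general health as a between-arm outcome from Table 2. This costs nothing in collection, and EQ-5D remains for all arms.

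If the outcome is kept, Table 2 should name SF-GH1 as the instrument rather than the SF-36.

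For activation, remove it from the list in the Outcomes section and keep the items for the comparison of participants with decliners and drop-outs described under Other measurements. This is a change of wording only.

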### Outcomes

The effects of using PRO as the basis for follow-up will be evaluated with regard to three different aspects: clinical outcomes, health resource utilisation and patient-reported outcomes. Clinical outcomes include pivotal clinical quality measures (mortality, renal function, initiation of dialysis, hospitalisation). Health resource utilisation will be measured by number of contacts to the nephrology outpatient clinic (Table 2) and the patient-reported outcomes will be measured with regard to: quality of life, illness perception, patient activation, satisfaction and confidence towards the outpatient follow-up. An overview of primary and secondary outcomes and data sources is shown in Table 2.

**Table 2 Tab2:** Primary and secondary outcomes, data sources and timeline for measurements

**Outcomes**	**Data source**	**Measurement/month**
**Clinical outcomes**		
Renal function (eGFR)	Electronic health record (EHR)	0,3,6,9,12,15,18
Mortality	Electronic health record (EHR)	6,12,18
Initiation of dialysis	Electronic health record (EHR)	6,12,18
Transplantation	Electronic health record (EHR)	6, 12,18
Hospitalisation	Electronic health record (EHR)	16,12,18
CKD biomarkers	Electronic health record (EHR)	0,3,6,9,12,15,18
**Resource utilisation**		
Number of face-to-face visits	Electronic health record (EHR)	6,12,18
Unexpected contacts	Electronic health record (EHR)	6,12,18
Phone contacts	Electronic health record (EHR)	6,12,18
**Patient-reported outcomes**		
Quality of life	Euroqol (EQ-5D 5 L)	0,6,12,18
General health	Short Form-36 (SF-36)	0,6,12,18
Illness perception	Brief Illness Perception (IPQ-B)	0,6,12,18
Self-efficacy	General Self-efficacy (GSE)	0,12,18
Patient involvement	AmbuFlex PRO questionnaire	6,12,18
Confidence, satisfaction	AmbuFlex PRO questionnaire	6,12,18

### Primary outcome

Loss of renal function measured as a change in eGFR is the primary outcome and is considered to be the most accurate single measurement for renal function assessment [34].

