Sample size was estimated for the primary outcome loss of renal function (eGFR). From literature review, the non-inferiority limit for eGFR is determined to be 2.85 mL/min/1.73 m^2^/year [49]. Based on a literature review, the assumptions are an approximate loss in eGFR of 5 mL/min/1.73 m^2^/year, SD: 4 mL/min/1.73 [49]. Loss in eGFR is normally distributed. Given 80% statistical power and *p*-value of 0.05, we need 50 patients in each group, in total 150 patients. With an estimate of 250 incident patients seen yearly, 150 patients will be reached in an inclusion period of 1 year and 2 months due to the expected attrition [50].

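### The non-inferiority limit is a rate per year, but the primary outcome is a change in eGFR with no time unit or time point, so the quantity tested is not tied to the scale of the margin

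*Protocol article*

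**What the plan says.** Four statements in the protocol article bear on the primary test.

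- **Outcome** (Primary outcome): "Loss of renal function measured as a change in eGFR is the primary outcome". No time unit or time point is given. The study timeline lists assessments at 6, 12 and 18 months and names none as primary. Table 2 schedules eGFR at months 0, 3, 6, 9, 12, 15 and 18.
- **Margin and assumptions** (Statistical methods, sample size paragraph): "the non-inferiority limit for eGFR is determined to be 2.85 mL/min/1.73 m^2^/year", and "the assumptions are an approximate loss in eGFR of 5 mL/min/1.73 m^2^/year". The spread is printed as "SD: 4 mL/min/1.73 [49", so its unit is cut short and carries no time.
- **Timing of measurement** (closing sentence of Patient-reported outcomes, which covers all outcomes): baseline and 6, 12 and 18 months, "or at the time a patient leaves the study due to patient wish, death, transplantation or initiation of dialyses".
- **Model** (Statistical methods, continuous endpoints, with eGFR as an example): differences in means with 95% confidence intervals, the primary analysis being covariate-adjusted "in a multiple linear regression model". No slope, annualisation or follow-up time is mentioned.

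**The concern.** A non-inferiority decision compares a confidence limit with a margin, so both must be on one scale. Here the margin is a yearly rate, while the outcome is a change over an unstated period that may differ between patients. Nothing connects the two.

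Two things are at stake. First, the strictness of the test depends on the period to which 2.85 is applied. Second, if values at exit enter as raw changes, patients who decline fastest and reach dialysis early are recorded with less loss than they would have had by month 18. Someone who leaves at month 6 has had 6/18, or one third, of the time in which to lose function. If an intervention arm truly declines faster, more of its patients are cut short in this way and the deficit shrinks toward zero, which is the unsafe direction in a non-inferiority trial.

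**Working it through.** **Inputs from the article:** margin 2.85 per year; expected loss 5 per year; SD 4 (per year is an inference); "Given 80% statistical power"; "value of 0.05, we need 50 patients in each group, in total 150 patients", with sidedness not stated. The 95% interval corresponds to one-sided 0.025.

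**1. The plan's own figure.** With no true difference, n per arm = 2 × [SD × (z₁₋α + z₁₋β) / margin]².
- One-sided 0.025: 2 × [4 × (1.960 + 0.842) / 2.85]² = 30.9, so 31.
- One-sided 0.05: 2 × [4 × (1.645 + 0.842) / 2.85]² = 24.4, so 25.

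The printed 50 does not follow without an unstated input. For example, 31/50 implies 38% attrition, and the article mentions attrition without a figure. That is a separate matter. It does mean that the printed sample size cannot show which scale was intended. If everything is per year, 50 per arm gives SE = 4 × √(2/50) = 0.80, and power Φ(2.85/0.80 − 1.96) = 94.5%.

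**2. What 2.85 means as a raw change.** Divided by the period in years, it is 2.85/0.5 = 5.7 per year at 6 months, 2.85 at 12 months, and 2.85/1.5 = 1.9 at 18 months. Keeping the yearly rate at 18 months requires 2.85 × 1.5 = 4.275.

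**3. Power with 50 per arm for a raw 18-month change** (one-sided 0.025, equal arms). The SD at 18 months is not in the article, so a range is shown.

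| Assumed 18-month SD | Power vs 2.85 | Power vs 4.275 |
|---|---|---|
| 4 (no growth) | 94.5% | >99% |
| 4.9 (4 × √1.5) | 82.9% | 99% |
| 6 (4 × 1.5) | 66.1% | 94.5% |

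**4. Effect of exit values.** Two illustrative simulations were run, each with the intervention worse by exactly 2.85 per year. The eGFR at which a patient exits is a modelling device, not a statement about when dialysis should start.

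- *Simulation A.* Baseline mean 25 (SD 7), slope SD 3.5 per year, visit error SD 2, exit at eGFR 8 or 10, 50 per arm, 4,000 runs. The true 18-month difference of 4.28 shrinks to about 3.3–3.65. Raw exit change against 4.275 gives false non-inferiority of about 8% (exit at 8) to 12–13% (exit at 10), where 2.5% is intended. The same raw change against 2.85 gives 0.3–0.7%, with power of about 70–71% when the arms are equal. A slope analysis by generalised least squares against 2.85 per year gives 2.6–2.8% false non-inferiority and 96% power.
- *Simulation B.* Baseline uniform 10–39, slope SD 4 per year, visit error SD 2. The difference of 4.27 shrinks to 3.42 (exit below 7; exits 18% control, 31% intervention) or 3.07 (exit below 10; 27% and 41%). With equal arms the difference stays at zero. Each patient's change divided by own follow-up time keeps the difference at 2.84–2.85 per year, but its SD in the control arm rises from 4.4 with no exits to 5.2 with exit below 10, because short follow-up gives noisy rates.

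**5. Gain from all seven values.** Under the inputs of Simulation A and full follow-up, the variance of a two-point annualised change is 3.5² + 2 × 2²/1.5² = 15.81. For a seven-point slope it is 3.5² + 2²/1.75 = 14.54, a saving of about 8%.

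**The case against.** A reader might infer that the test is on the wrong scale and is biased by early dialysis. The article does not support that.

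- It never says that the change is un-annualised, and it does not name 18 months as the primary time point. The sample size paragraph concerns the same outcome and speaks of loss per year, so an annualised loss is a natural reading.
- The regression paragraph is generic. Its response could be a per-patient slope or an annualised change, and Table 2 lists all seven eGFRs, so it cannot be said that only two are used.
- The exit sentence sits under patient-reported outcomes and says when data are collected. It does not say that an exit value stands in for a month-18 value.
- The 8–13% needs raw changes, exit values and a rescaled margin together, and the rescaled margin is not in the article. With the printed 2.85 the same raw change is conservative. The two distortions belong to alternative readings and act in opposite directions.
- Patients with projected end-stage disease within 12 months are excluded, and dialysis and mortality have their own time-to-event analyses.

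All of this stands, and it limits the claim to a scale that is not fixed. It does not remove the point. The exit sentence covers all outcomes, follow-up runs beyond the 12 months of the exclusion, and patients with eGFR down to about 10 are eligible. The article does state an outcome, an exit timing, a model and a threshold, and together they do not yield a quantity on the threshold's scale. That goes beyond detail ordinarily left to an analysis plan.

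**Conclusion.** The point holds as a mismatch that must be reconciled: a yearly margin is attached to a change with no defined period. Only the scale arithmetic (1.9 per year, or 4.275 over 18 months) follows from the article alone.

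The consequences depend on the reading:

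- **Raw 18-month change against 2.85:** the test is stricter than intended. Power with 50 per arm is about 66–71% if the SD grows in proportion to time or as in Simulation A, 83% if it grows with the square root of time, and unchanged at 94.5% if the SD of 4 already describes the 18-month change.
- **Raw exit changes against 4.28:** a true 18-month deficit of 4.28 appears as about 3.1–3.7, and false non-inferiority is about 8–13%. This rests on assumed baseline eGFR, slope spread, visit error and exit level. It arises only when the arms truly differ and is zero when they are equal.
- **Annualised change or slope:** consistent with the margin.

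This is the trial's single primary test, so the choice should be fixed before any comparative eGFR data are examined.

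**What to change.** Define the primary outcome as the between-arm difference (intervention minus control) in annual eGFR slope, in mL/min/1.73 m² per year, from randomisation to month 18. Estimate it for each intervention arm against usual care with a linear mixed model (random intercept and slope, arm-by-time term, the planned covariates) on all scheduled eGFRs up to dialysis, transplantation, death or withdrawal. Declare non-inferiority if the lower 95% limit is above −2.85 per year. State the SD on the same per-year scale. A joint model of slope and dropout can be added as a sensitivity analysis.

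Per-patient annualised change, or a change at one fixed time with margin and SD on that scale, would also remove the mismatch. The first is noisier after early exit, and the second still needs a rule for patients who leave before that time.

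The cost is wording and some programming, since the seven eGFRs are already scheduled. The small downside is that decline is assumed to be roughly linear over 18 months.
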